## Abstract

**Background:**

Universal tobacco-prevention programs targeting youths usually involve significant adults, who are assumed to be important social influences. Commitment not to use tobacco, or to quit use, as a formal contract between an adolescent and a significant adult is a preventive model that has not been widely practiced or explored and has been formally evaluated even less. In this paper, we present the rationale and protocol for the evaluation of the Swedish Tobacco-free Duo program, a multicomponent school-based program the core of which rests on a formal agreement between an adolescent and an adult. The adolescent’s commitment mainly concerns avoiding the onset of any tobacco use while the adult commits to support the adolescent in staying tobacco free, being a role model by not using tobacco themselves.

**Objective:**

To assess (1) whether Tobacco-free Duo is superior to an education-only program in preventing smoking onset among adolescents and promoting cessation among their parents, (2) whether exposure to core components (adult-child agreement) entails more positive effects than exposure to other components, (3) the impact of the program on whole school tobacco use, (4) potential negative side effects, and (5) school-level factors related to fidelity of the program’s implementation.

**Methods:**

A mixed-design approach was developed. First, a cluster randomized controlled trial was designed with schools randomly assigned to either the comprehensive multicomponent program or its educational component only. Primary outcome at the adolescent level was identified as not having tried tobacco during the 3-year junior high school compulsory grades (12-15 years of age). An intention-to-treat cohort-wise approach and an as-treated approach complemented with a whole school repeated cross-sectional approach was devised as analytical methods of the trial data. Second, an observational study was added in order to compare smoking incidence in the schools participating in the experiment with that of a convenience sample of schools that were not part of the experimental study. Diverse secondary outcomes at both adolescent and adult levels were also included.

**Results:**

The study was approved by the Umeå Regional Ethics Review Board (registration number 2017/255-31) in 2017. Recruitment of schools started in fall 2017 and continued until June 2018. In total, 43 schools were recruited to the experimental study, and 16 schools were recruited to the observational study. Data collection started in the fall 2018, is ongoing, and is planned to be finished in spring 2021.

**Conclusions:**

Methodological, ethical, and practical implications of the evaluation protocol were discussed, especially the advantage of combining several sources of data, to triangulate the study questions. The results of these studies will help revise the agenda of this program as well as those of similar programs.

**Trial Registration:**

International Standard Randomized Controlled Trial Number (ISRCTN) 52858080; https://doi.org/10.1186/ISRCTN52858080

**International Registered Report Identifier (IRRID):**

DERR1-10.2196/21100

## Introduction

Social influences, such as smoking parents, siblings, or friends, are the strongest determinants of smoking initiation in adolescence [1,2]. In practice, one may conceptualize smoking initiation as a socially learned behavior, while the subsequent trajectories leading to escalation or to extinction of smoking behavior are determined by a more complex mixture of reinforcing or weaning factors, including genetics, psychosocial circumstances, and availability of tobacco products [3].

According to Bronfenbrenner’s theoretical frame [4], people in close microenvironments are likely to exert the strongest health-related influences (in this case pro or antismoking), at least in early adolescence and during initial episodes. Peers normally exert a direct and proximal influence by creating the context for smoking to occur; in fact, the association of friends or siblings smoking is in many cases stronger than that of parents smoking [5]. Adult influences, on the other end, are conveyed on a broader frame. First, adults may shape opinions and attitudes over developmental years by simply tolerating or not explicitly disapproving of smoking [6]. Smoking behavior among significant adults may further encourage the onset of smoking in adolescence by creating an implicitly favorable norm [7]. Availability of cigarettes with or without permission is high in environments where adults smoke [8], which is an important facilitating factor when purchase is not affordable as it is the case among adolescents, a price sensitive group [9]. Also, the possibility that early exposure to environmental smoking primes the child’s brain to the rewarding properties of nicotine has been presented [10].

Importantly, social influence seems to extend to tobacco uses other than smoking, at least in countries where other established forms of tobacco use exist, as is the case in Sweden, where the use of the oral moist tobacco snus is widespread among men [11].

For these reasons. adult influences (and parents’ influences, in particular) are usually regarded as an important cue in universal prevention of tobacco use.

Consistent with these observations, youth smoking prevention programs in different settings have often included some degree of parental involvement [12]. Despite promising indications that adding a family component increases the effectiveness of school-based programs, the findings of studies have not been consistent [13]. Some encouraging evidence exists on using public commitment as a strategy for prevention. In a systematic review [14] of school-based smoking prevention programs, there was a significant effect of programs including commitments to not smoke. A community-wide school-based intervention program aimed at preventing adolescent tobacco use, incorporating public commitment activities as one of several components, led to a reduced smoking in those who initiated smoking [15].

A component of public commitment has been successfully included in a variety of public health programs and target groups. For instance, in programs using life skills training to prevent drug use, some positive results have been found when including this component [16]. In a school-based diabetes prevention project, there was a suggestion that a public commitment to a healthy lifestyle was associated with a lower prevalence of obesity at follow-up [17]. Some support has also been found for interventions using public commitment as a strategy in adult smoking cessation, including the use of contracts in general practitioner-led interventions [18].

Concerning smoking prevention in youths, a comprehensive social influence program including a decision-making component was found to be effective in a randomized trial [19] for students aged 13-15 years. An evaluation of a prevention program against substance use and other problem behaviors among adolescents in grade 9 using a contract as a component reported small to moderate differences in substance use between groups based on length of participation in the prevention program; however, limitations in the study design made it difficult to draw firm conclusions [20]. A school-based smoking prevention program called the Smoke Free Class competition was introduced in more than 20 European countries during the years 1997-2009. The program included a commitment to not smoke and prize draws. The program was evaluated by randomized controlled trials in several countries, and a meta-analysis [21] reported that the program seemed to be effective in preventing smoking.

The Swedish program *Tobacco-free Duo* is an example of this category of programs, addressing all forms of tobacco use. Details on the intervention and on its preliminary evaluation have been published [22-24]; however, firm conclusions on favorable effects of the intervention could not be reached due to weak study design or to methodologic shortcomings in these earlier evaluations. The Public Health Agency of Sweden commissioned this evaluation in order to strengthen the evidence base to be incorporated in possible future recommendations.

This commission was translated into the following specific objectives: (1) to assess whether the comprehensive Tobacco-free Duo program is superior to an education-only program in preventing onset of use of cigarettes or other tobacco among adolescents or in fostering smoking cessation among smoking parents, (2) to assess whether the adolescents or parents exposed to the core component of the program (adult-child agreement) refrained from using tobacco to a higher extent than those who were only exposed to other components of the program, (3) to explore the impact of the program on the whole school tobacco use prevalence over time, (4) to understand whether receipt of the program entailed negative side effects on the participating adolescents, and (5) to analyze school-level factors related to fidelity of the program implementation.

A health economic evaluation (cost-effectiveness study) will be conducted alongside the randomized controlled trial, and its corresponding protocol will be the object of a separate publication.

## Methods

### Intervention

#### Overview

The Tobacco-free Duo is a complex intervention for the universal prevention of tobacco use developed in Sweden and in use since 1993, starting from the County of Västerbotten in the North of Sweden. From 2007, the intervention has also been adopted in other counties, by request of the regional government or by request of the individual municipalities or schools, therein. About 80 municipalities are known to have implemented the Tobacco-free Duo program [25].

#### Components

In brief, the program aims to mobilize antitobacco practices and attitudes in adolescents’ near environments, with schools as main promoters and arenas for the activities. The recommended starting point is in the sixth or seventh grade of compulsory school (between 12 and 13 years of age), and it encompasses 6 central components that were manualized in this study.

The tobacco-free pair (Duo) core component that is the origin of the program’s name consists of an agreement between an adolescent and a significant adult (at least 18 years old) elected as partner by the adolescents. The pair agrees to remain tobacco free during the following 3 years, at least, until the index adolescent leaves the compulsory school (about 15 years of age). The written agreement is signed by both partners, possibly during a public event in school, strengthening the mutual commitment. However, a pair can be formed anytime during the school year.Student information is given by a member of the school staff who informs the student in the sixth or seventh grade about the school choice to adopt the program, briefly discusses tobacco control issues, and actively encourages participation of the adolescents.Parent information is given during an ordinary parent meeting at school where they are given access to information and materials explaining their role in tobacco prevention and how they can actively support their children in their commitment.As an incentive to participate, all adolescents signing a contract will receive a membership card that entitles them to some fringe benefits in local shops or leisure-time activities.At the end of each school year, the pairs disclose and confirm their tobacco-free status. The disclosure entitles the index adolescent to participate in a lottery taking place just before the summer break.Interactive classroom education is conducted by trained school personnel in all classes during grades 6 (or 7) to 9. This education consists of age-specific information and practical exercises (eg, how to identify and resist social influences). For the purpose of this evaluation, the educational part was further structured and manualized before training personnel.

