**Objective 1**			
	Questions 1 and 3		Is the probability of having never smoked (question 1) or used any tobacco product^a^ (question 3) at the end of follow-up in the ninth grade higher for seventh-grade adolescents in schools assigned to the full program (Tobacco-free Duo components 1-6) compared to that of adolescents in schools assigned to conduct only the educational component (component 6)?
	Questions 2 and 4		Is the probability of never having progressed to regular (weekly during at least 3 consecutive months) use (question 2: smoking cigarettes; question 4: any tobacco product) by grade 9 higher for adolescents in Tobacco-free Duo schools than for those in education-only schools?

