#### Training of School Personnel

School staff involved in the study are offered an annual meeting with education, training, and networking in their respective experimental group (Tobacco-free Duo school or education-only school). The content of the meeting is diversified according to the assigned intervention, with a common part regarding instructions for data collection and the educational intervention component. The aim is to gradually increase the personnel’s knowledge, to give an opportunity for exchange of experiences during the project period, and assure quality of data collection over time. The meetings are scheduled to be held annually before the fall term start, separately for education-only and Tobacco-free Duo schools.

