Participating students in schools randomized to Tobacco-free Duo or education only	Paper questionnaire, with information on: Cigarette and snus use (any, current, frequency, quitting) Tobacco use among friends and family members Received education, knowledge and attitudes toward tobacco Recent and current use of alcohol Ever use of illicit drugs General health, physical activity, and sedentary time Perceptions about the contract (if appropriate)	Self-administered in the classroom	Unique study code matched to identity information	Baseline: fall term of school year 1- grade 7 Follow-up 1: end of school year, grade 7 Follow-up 2: end of school year 2, grade 8 Follow-up 3: end of school year 3. grade 9
Guardians of the participating students above	Paper questionnaire, with information on: Sociodemographics Relation with the index child and perception of risks with tobacco use Own tobacco and alcohol use	Self-administered at home	Same code as the index child above	Same time points as above
Adults in Tobacco-free Duo pairs	Paper questionnaire, with information on: Own use of cigarette and snus Perception of own role in the intervention	Self-administered at home	Same code as the index child above	Anytime a contract is signed
All students registered in Tobacco-free Duo schools, education-only schools and reference group schools in grades 7-9	Paper questionnaire, with information on: Ever, regular and recent use of cigarette and snus	Self-administered in the classroom	No identifier (anonymous survey)	Cross-sectional surveys at the end of school year 1, 2 and 3

Figure 1 displays a scheme of the participants’ enrollment and assessments time-points for the experimental part of the study.

Individual data from questionnaires will be optically scanned, and the corresponding electronic files will be stored in a password-protected section of the server at the Department of Global Public Health, Karolinska Institutet. In order to preserve strict confidentiality, this data will be stored without personal identifiers, substituted by a study code unique to each participant. Personal identifiers will be kept in a separate section of the same server, only accessible to 2 members of the study team, responsible for data linkage and follow-up procedures, respectively. Ten years after the study start the personal identifiers will be removed and all information will be kept identified only through the study code.

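### In Duo schools, contract signers declare themselves tobacco free for a lottery in the same end-of-year window as the identity-coded outcome questionnaire, giving them an indirect, arm-specific motive to deny smoking

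*Protocol article*

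**What the plan says.** All references are to the Protocol article.

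- **Components.** The full program includes a yearly declaration: "At the end of each school year, the pairs disclose and confirm their tobacco-free status". Its consequence follows: "The disclosure entitles the index adolescent to participate in a lottery taking place just before the summer break". Signing carries a separate benefit: "all adolescents signing a contract will receive a membership card that entitles them to some fringe benefits in local shops or leisure-time activities".
- **Table 1, Objective 1.** The Duo schools' result is "compared to that of adolescents in schools assigned to conduct only the educational component (component 6". The comparator therefore has no contract, card, declaration or lottery.
- **Table 2.** The primary outcome is a negative answer to a single question on ever having tried smoking, even a few puffs.
- **Table 3.** The trial cohort answers on paper, in the classroom, under a "Unique study code matched to identity information". The decisive round is "Follow-up 3: end of school year 3. grade 9". A separate survey of all students in grades 7 to 9 runs at the end of years 1, 2 and 3 and is marked "No identifier (anonymous survey").
- **Training of School Personnel.** The yearly staff meetings are held separately by arm, "with a common part regarding instructions for data collection and the educational intervention component".
- **Data Collection and Management.** Scanned answers are stored without personal identifiers. The identifiers are kept apart and are open to two study-team members only.
- **Randomization.** Participants cannot be blinded.
- **Data Analysis.** The sensitivity analyses listed deal with missing outcomes.

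**The concern.** A student who signs a contract and later tries smoking has both had the outcome event and broken the agreement. To stay in the lottery, that student confirms tobacco-free status at the end of the year. In the same part of the year the student is asked in class, on a form carrying a personal code, whether he or she has ever tried smoking. An honest answer contradicts the declaration. A student in an education-only school who has tried smoking has made no declaration to contradict.

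This differs from ordinary under-reporting, which would affect both arms alike and mainly dilute the comparison. Here the pressure exists in one arm only and favours Duo. Randomization and intention-to-treat analysis do not correct outcome misclassification that differs by arm. The as-treated comparison of signers with non-signers would be affected more, because there the motive applies to every member of one group.

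**Working it through.** **1. The plan's own figures** (Estimation of Sample Size). Control prevalence of never smoking is 0.70 and the target risk ratio is 1.10, so the Duo target is 0.70 × 1.10 = 0.77, a difference of 7 points. The share of controls who have tried smoking is 1 − 0.70 = 0.30. The design effect is 1 + (50 − 1) × 0.02 = 1.98, as stated.

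Two-sided 5% and 80% power need 623 per arm, 1246 in total. Then 1246 × 1.98 = 2467, and 2467 / 0.80 = 3084. This is within 3% of the stated 3000, so the inputs are being read as intended. (Dividing also by 0.92 gives 3352. The point below does not depend on this.)

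**2. Arm-wide bias with no true effect.** Let *u* be the share of Duo triers who deny smoking in excess of controls. The documents give no value, so *u* is an assumption shown as a range. The apparent Duo prevalence is 0.70 + 0.30 × *u*.

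For the chance of a significant result favouring Duo, take 3000 × 0.92 × 0.80 = 2208 analysed. The effective size is 2208 / (2 × 1.98) = 558 per arm, tested two-sided at 5%. (The article does not state whether the test is one- or two-sided.)

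| *u* | Apparent Duo prevalence | Apparent difference | Risk ratio | Chance of a significant result for Duo |
|---|---|---|---|---|
| 0 | 0.700 | 0 | 1.00 | 2.5% |
| 5% | 0.715 | 1.5 points | 1.02 | 8% |
| 10% | 0.730 | 3.0 points | 1.04 | 20% |
| 20% | 0.760 | 6.0 points | 1.09 | 62% |
| 23.3% | 0.770 | 7.0 points | 1.10 | 75% |

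The value that reproduces the whole target is 0.07 / 0.30 = 23.3%. The significance threshold is 1.96 × √(2 × 0.70 × 0.30 / 558) = 5.4 points, which corresponds to *u* of about 18%.

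**3. Dilution by signing.** The motive applies to contract signers only. If a share *s* of Duo triers are signers, the denial needed among signers to create the whole target effect is 0.233 / *s*. The value of *s* is also not given.

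| *s* | Excess denial needed among signers |
|---|---|
| 30% | 78% |
| 50% | 47% |
| 70% | 33% |
| 90% | 26% |

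**4. Timing and available checks.** Table 3 and the Components section use the same label for the questionnaire and the declaration: the end of the school year. The text does not say which comes first. The anonymous survey covers grade 9 in both arms at the end of year 3 and asks about ever use, but it is assigned to Question 7, a trend in prevalence over grades 7 to 9, and not to checking the identified answers.

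**The case against.** Much of the opposing case stands.

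- **No reward depends on the outcome form.** The lottery depends on the pair's declaration and the card on signing. A reader might infer that Duo students are rewarded for denying smoking on the trial questionnaire. The text does not support that: nothing says the answers reach the school, the partner or the lottery. What remains is an indirect motive.
- **There are safeguards.** Self-completion, coded storage and separated identifiers lessen the fear of being identified. Who supervises the classroom session and collects the forms is not stated, so it cannot be assumed that school staff read them.
- **Only signers are affected.** The plan expects non-signers and drop-out from contracts, and students who try smoking may be less likely to hold a contract.
- **An anonymous between-arm comparison is already planned.** A reader might infer that a positive result could never be told apart from denial. That goes too far, since Question 7 compares Duo and education-only schools on anonymous data. It pools grades, however, and is not set up as a reporting check.
- **The order may already be right.** The year-end label is coarse, and the field manual or the full plan may place the questionnaire first.

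The argument that all of this belongs in documents not shown carries less weight. The article itself fixes the timing, setting and identifiability of the outcome and the timing of the declaration, and as written these share a window. Confidential storage does not change what a student feels while filling in a coded form in class.

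**Conclusion.** The concern holds as an indirect, arm-specific reporting motive among contract signers that would favour Duo on an unblinded, self-reported primary outcome. Its size cannot be determined from the documents.

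On assumed arm-wide excess denial of 5% to 23%, the apparent effect runs from 1.5 to 7.0 points against a 7-point target. It is tempting to read the upper figure as denial by under a quarter of signers. It is an arm-wide rate: with 50% or 70% of Duo triers signing, 47% or 33% of signers would have to deny. Smaller rates still raise the chance of a false positive.

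These results assume no true effect, control prevalence of 0.70, 2208 analysed students, a design effect of 1.98 and a two-sided 5% test. This should be fixed, because the remedy is cheap and the bias runs one way. The trial is not invalid without it.

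**What to change.** 1. **Order and wording.** Give the identified follow-up questionnaire before that year's disclosure and lottery, in the same calendar window in both arms. State on the form that answers are not seen by the school and are not used for contract, card or lottery. This reduces the motive but does not remove it, because the contract and earlier years' declarations persist. It can apply only to rounds not yet held; the article plans the last for spring 2021.

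2. **A pre-specified supportive analysis.** From the anonymous year-3 survey, estimate the Duo versus education-only difference in grade-9 never-smoking. Also estimate the between-arm difference in the gap between identified and anonymous prevalence: (identified − anonymous) in Duo minus (identified − anonymous) in education-only. Give each with a cluster-adjusted confidence interval, beside the primary result. For this check, compute the identified prevalence on all cohort members, not only baseline never-smokers, because the anonymous survey cannot exclude baseline smokers.

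3. **Interpretation.** Read the gap with its interval. Do not declare inflation merely because the gap is larger in Duo schools: without any bias, chance would produce that about half the time. State that the two populations differ (non-consenting students are in the survey only; students who changed school are followed in the cohort). State also that the anonymous form is completed in class at year end, so similar gaps in the two arms would not rule out denial.

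The cost is one scheduling constraint at the end of term and one extra table from data already being collected.
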